## Abstract

**Background:**

Despite the effectiveness of psychosocial programs for recovery from drug use problems, there have been challenges in implementation of treatment. Internet-based and computerized approaches have been known to be effective in treatment dissemination. The study purpose is to assess the effects of a web-based psychosocial relapse prevention program with a multicenter randomized controlled trial.

**Methods:**

Recruitment began in January 2015 for outpatient participants diagnosed with drug abuse or dependence who have used a primary abused drug in the past year at psychiatric hospitals and a clinic. Participants are randomized either to a web-based relapse prevention program or a self-monitoring group. The intervention is a web-based relapse prevention program named “e-SMARPP” that consists of six relapse prevention program modules with tailored feedback from health care professionals and 8 weeks of self-monitoring. The content is adapted from a face-to-face relapse prevention program which is based on cognitive behavioral therapy and motivational enhancement. The primary outcomes are relapse risk assessed by the *Stimulant Relapse Risk Scale* (baseline, 2-, 5- and 8-month) and the longest duration of consecutive abstinent days from primary abused drug during the intervention. Secondary outcomes will include motivation to change, self-efficacy for drug use and craving, abstinent days in the past 28 or 56 days, quality of life, sense of coherence, cost of substance use, medical cost, retention of treatment and use of self-help group. Completion, usability and satisfaction of the program will be also assessed to explore feasibility. This study protocol was approved by the Ethics Committee of The University of Tokyo and each recruiting hospital and clinic.

**Discussion:**

To our knowledge, this study is the first clinical trial to assess the effects of a web-based therapeutic program for drug users in Japan. If successful, this program is a promising approach for drug user treatment in Japan, where the stigma toward drug users is strong. The results are also useful for researchers who want to know about programs for various substances, including methamphetamine.

**Trial Registration:**

This trial was registered with the University Hospital Medical Information Network clinical trial registry: UMIN000016075 (Date of registration: January 5, 2015).

## Background

### Drug use problems and implementation of treatment

Drug use problems have been a serious public health concern and illicit drug dependence is a global burden, accounting for 0.8 % of global all-cause disability adjusted life years in 2010 [1]. Drug dependence is highest in the age cohort of 20–29 years and adversely affects young adults [1, 2]. In Japan, drug use prevalence and drug related health problems have been much lower than that of other countries [3–5]. However, methamphetamine use disorders are the most prevalent in drug addiction treatment. Moreover, problems related to prescription drug use and overdose are serious, especially in Japanese female patients [6–8]. Moreover, outpatient treatment and community-based support for drug users have been very poor because of a zero-tolerance policy [6]. Accessible psychiatric treatment use is very limited, accounting for about 16 % of drug/alcohol use disorders [9]. Because pharmacotherapy for drug dependence (e.g., methadone, buprenorphine) has not been approved in Japan, psychosocial approaches are the most important treatment, especially in outpatient settings. However, there has been a gap between potential treatment needs and available treatment services, which is also apparent in other countries. Various reasons have been considered as barriers to treatment access: (1) limited availability (e.g., rigid session times, inconvenient locations, costs for drug users), (2) concerns about confidentiality and stigmatization and (3) economic and human-resource limitations for treatment providers [10–14]. Flexible and accessible treatments are necessary, especially in Japan as outpatient treatment for drug users is very limited and societal drug-use stigma is strong.

### Treatment using computer and Internet technologies

Therapeutic interventions using computer and Internet technologies have developed and adapted to various health problems, including substance use disorders, to address challenges in treatment implementation [15–17]. Many computer-assisted or web-based interventions for drug users which were developed based on psychosocial approaches demonstrated benefits for abstinence, treatment retention and cost effectiveness with small to moderate effect sizes [10, 11, 18–22]. Most of these interventions have been developed for cocaine or cannabis users in Western countries. There are few programs for amphetamine-type-stimulant users and for populations in Asia with different social backgrounds, even when Internet infrastructure and computers are generally available [23, 24]. In Japan, there have been various web and mobile applications to assist in personal health care, however, evidence-based therapeutic interventions for drug users remains undeveloped.

### Previous work: development of “e-SMARPP”

A new piloted web-based program named “e-SMARPP” for Japanese drug users was developed by the first author (AT) based on an existing face-to-face cognitive behavioral relapse prevention program [25], using Moodle (version 2.6.1) which is an open-source web application to build e-learning websites [26]. A referenced program was the Serigaya Methamphetamine Relapse Prevention Program (SMARPP), which was developed based on the Matrix Model by one of the authors (TM) and was widely implemented in Japan [25]. The web-based e-SMARPP program consisted of three parts: a relapse prevention program series that included videos, with narration and subtitles, and assignments in the form of exercises and a diary; self-monitoring; and information about drug addiction services. e-SMARPP content is intended to be user-friendly with minimal text and limited use of difficult Kanji characters referencing specialized medical terminology. User guides in each section support use. The e-SMARPP website is designed to support any device, including personal computers, mobile phones and tablet computers with Internet access. The website is closed access and only drug users diagnosed with drug dependence by psychiatrists are provided a login account from an administrator. The access security is protected by an individual login/password and secure socket layer technology. The content of e-SMARPP does not depend on the type of drug and was developed with versatility to assist in handling common problems among drug users. This was because most face-to-face programs for drug users deal with problems of various drugs and it was not feasible to gather homogeneous patients in Japan. The usability and acceptance of e-SMARPP were reasonable among psychiatric outpatients and people who had recovered from drug dependence, but some improvements were suggested [25]. Details of the development process and findings of the pilot study were reported in a previous study [25]. In the revision process after the piloted usability test, content of the videos were simplified to focus on approaches to recovery rather than drug adverse effects. Self-monitoring was improved to be able to record detailed conditions about drug users if necessary (e.g., drug consumption, forms of used drugs, triggers of drug use). Functional defects including garbled characters on mobile phones were fixed.

### Objectives and hypotheses

The aim of this study is to examine the effects of a web-based cognitive behavioral relapse prevention program, revised as e-SMARPP, among Japanese psychiatric outpatients with methamphetamine and other drugs use problems with a multicenter randomized controlled trial (RCT) design. The primary hypothesis is that participants assigned to e-SMARPP will have reduced relapse risk and maintain a longer duration of consecutive abstinence (days) from a primary abused drug during the intervention compared to those who were randomized to self-monitoring only. The secondary hypothesis is that participants in the e-SMARPP group will report positive changes in motivation to change, self-efficacy for drug craving, abstinent days in the past 28 or 56 days (percentages and differences in change: pre-post), quality of life, sense of coherence, cost of alcohol and drug, retention of treatment, use of self-help group and psychiatric medical cost. In addition, completion, usability and satisfaction of the program will be assessed for utilization and feasibility test. This article describes the study protocol according to SPIRIT guidelines [27].

## Methods

### Trial design

Figure 1 shows the design of this study and participant flow. This study is a two-arm (allocation ratio is one to one), parallel-group, non-blinded and multicenter randomized controlled trial. Eligible participants are asked to complete the baseline assessment and are randomly allocated to either the intervention group or the control group. All participants in both groups will be provided a login/password with instructions about how to access the website and use e-SMARPP during the study. The participants in the intervention group can access the complete contents of e-SMARPP, while the control group can access a part of it: self-monitoring. Each individual access account is tied to either group, and as such participants can use e-SMARPP content included in their group only. Web-based follow-up assessments are conducted at 8, 20, 32 weeks after the baseline assessment.

**Fig. 1 Fig1:**
[figure not shown]
Study design and participant flow

### Participants and setting

The participants are recruited from five psychiatric hospitals and one clinic (National Center of Neurology and psychiatry, Saitama Psychiatric Medical Center, Kanagawa Psychiatric Center, Okayama Psychiatric Medical Center, Tokyo Metropolitan Matsuzawa Hospital and APARI clinic) that provides treatment for people with substance use disorder in Japan. The inclusion criteria are: (1) outpatients who were diagnosed with substance use disorder assessed by DSM-5 (psychoactive substances other than alcohol and tobacco), (2) those who used a primary abused drug in the past year and (3) those with access to the Internet via PC, smartphone or tablet computer and can exchange e-mail. The exclusion criteria are: (1) patients with severe physical diseases, (2) patients with high suicide risk, (3) patients with severe symptoms of substance-induced psychotic disorder, (4) patients with impaired cognitive function and (5) those who judged ineligible to participate in the study by a psychiatrist. We include various types of participants (form of drugs, previous and current receiving treatment for drug dependence, psychiatric comorbidity, pharmacotherapy and sexual orientation) because we will test adaptation of e-SMARPP to various drug users in a secondary analysis.

### Randomization and blinding

Staff of recruiting institutions will recruit outpatients who meet inclusion criteria. Eligible participants will be informed that they will be allocated to either of the two groups. After baseline assessment, they will be randomly assigned to either of the two groups using the method of permuted block, with random block size of four, and they will be informed their assigned group by the first author (AT). Randomization will be stratified by institution. The computer-generated allocation list was made by an independent researcher (YM) and concealed to other researchers and participants until the time of assignment. The enrollment is conducted by the first author (AT) and the intervention starts immediately. Researchers and staff who work for recruiting institutions will be blinded. In addition, an independent researcher (YM) who will not analyze data will download data from the e-SMARPP database and an independent research staff person will mask the group variable before analysis, then researchers (AT and [name]) will analyze data that is blinded to the group variable.

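### The plan names a single block size of four; if it is fixed within institution, the investigator who takes consent, enrols and announces groups can deduce about one third of assignments

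*Protocol article*

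**What the plan says.** All places are in the protocol article.

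- **Method.** Randomization and blinding assigns participants after baseline assessment, "using the method of permuted block, with random block size of four". It adds: "Randomization will be stratified by institution".
- **Sites.** Participants and setting: "The participants are recruited from five psychiatric hospitals and one clinic", so six strata.
- **Design.** Trial design describes a 1:1, "parallel-group, non-blinded and multicenter randomized controlled trial".
- **Who does what.** Randomization and blinding says of participants that "they will be informed their assigned group by the first author", and also: "The enrollment is conducted by the first author". Research ethics and approval has the same person take face-to-face consent. The Interventions section names that person as the main writer of feedback to the intervention arm.
- **Safeguards.** An independent researcher made the list, which stays hidden from other researchers and participants until each assignment. Site staff recruit patients, and researchers and recruiting-site staff are described as blinded. Participants and setting leaves the discretionary exclusion to a psychiatrist. The group variable is masked before analysis.

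**The concern.** A block size that is random cannot also be one number. The phrase may mean randomly permuted blocks of a fixed size four, or varying sizes of which only one was printed. The first is the more natural reading, and it matters because of who enrols.

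Hiding the list protects the next assignment only from someone who cannot work it out. The first author learns every earlier assignment at each institution by announcing it, and the block size is printed in that author's own article. The statement that researchers are blinded cannot apply to the person who announces each group. Masking the group variable protects the analysis, not enrolment.

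Someone who can foresee the next assignment could, even without intending to, let it influence how consent is discussed or when a patient is enrolled. The participants vary widely by design: the subgroup section spans baseline abstinence from under 1 month to 7–12 months. Such influence could therefore shift prognosis between arms. The outcomes are self-reported. The t-test of longest consecutive abstinence has no baseline adjustment, so an imbalance would pass straight into that co-primary result. The SRRS model does include the baseline score.

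**Working it through.** The plan gives no figure for predictability, so there is none to reproduce. Its total of 200 serves only as the denominator.

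**Inputs.** Block size 4, ratio 1:1, stratification by institution (Randomization and blinding; Trial design); six sites (Participants and setting); N = 200 (Sample size). Assumptions: blocks are fixed at four, the enrolling investigator tracks past assignments by site, and sites recruit equally.

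**Step 1: determined assignments in a complete block.** There are 6 equally likely sequences of two A and two B, giving 6 × 4 = 24 positions. A position is determined once one arm has used both its places.
- AABB and BBAA: positions 3 and 4 are determined, 2 × 2 = 4.
- The other four sequences: position 4 only, 4 × 1 = 4.
- Share = 8/24 = 1/3. By position: 0, 0, 1/3, 1.

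**Step 2: best-guess success in a complete block.** Guess the arm that is behind, and toss a coin when level.
- Position 1: 1/2. Position 2: 2/3. Position 3: 1/3 × 1 + 2/3 × 1/2 = 2/3. Position 4: 1.
- Sum = 17/6, and (17/6)/4 = 17/24 = 70.8%, against 50% without blocking.

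**Step 3: number of participants.**
- All blocks complete: 200 × 1/3 = 66.7.
- Four sites of 33 and two of 34: each site has 8 complete blocks plus one or two participants in positions that are never determined. That gives 6 × 8 × 4/3 = 64, and 64/200 = 32%.
- Best guess at a site of 33: (8 × 17/6 + 1/2)/33 = 70.2%.
- With site totals varying at random around equal recruitment, simulation gave a mean of 32% (range 31% to 33%).

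**Step 4: what varying sizes would achieve.** Simulation with 33 participants per site and equally likely sizes. The enroller is assumed to know the possible sizes but not their order.

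| Block sizes | Known with certainty | Best-guess success | Maximum imbalance within a site |
|---|---|---|---|
| 4 fixed | 32% | 70% | 2 |
| 2, 4, 6 | 4% | 69% | 3 |
| 4, 6 | 6% | 68% | 3 |
| 4, 6, 8 | 2% | 67% | 4 |

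The maximum imbalance is half the largest block. Varying the size removes nearly all certain knowledge but lowers guessing only a little, because guessing the arm that is behind needs no knowledge of block size. Including size 2 leaves guessing almost where it was.

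**The case against.** The strongest reply is that the one third depends on one reading of an unclear sentence. If sizes varied and were hidden from the enrolling investigator, the figure does not apply. This stands, and the conclusion is therefore conditional. The sentence would still need correcting, since it names one size.

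Second, the first author is not described as choosing the patients. Site staff described as blinded recruit, and a psychiatrist judges eligibility. This also stands. A reader might infer that eligibility itself is open to steering, but the text gives little support for that. What remains is consent and the timing of enrolment, both in one person's hands.

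Third, a reader might infer that any resulting bias could be neither seen nor removed later. The documents do not support that. Days since last use, 28-day drug use, DAST-20, SRRS and SOCRATES motivation are all collected at baseline. Steering on these factors could show in a baseline comparison and be adjusted for. Steering on unmeasured factors could not.

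Fourth, assignment already follows baseline assessment, and signed consent is required from all participants. That order is sound, but it does not stop someone deducing the next assignment before consent is sought.

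**Conclusion.** The point holds conditionally. The sentence on block size is ambiguous. If blocks are fixed at four within institution, an expected one third of assignments, about 64 to 67 of 200, can be deduced by the person who takes consent, enrols and announces groups. Best-guess success is about 70%. The figures rest on fixed blocks of four, tracking of past assignments by site, and equal recruitment at six sites.

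A reader might go further and conclude that a third of assignments are in fact known beforehand, or that selection took place. Neither follows: the documents show that assignments could be deduced, not that anyone did so. The exposure is mainly at consent and timing of enrolment, and the unadjusted t-test of longest abstinence is the more exposed of the two primary analyses. This should be put right while enrolment continues.

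**What to change.** 1. Correct the sentence in Randomization and blinding to state what was done: blocks of fixed size four, or sizes that vary at random.
2. If the size was fixed, have the existing independent researcher generate new within-institution lists for all remaining allocations, with randomly varying sizes, for example 4, 6 and 8. Do not disclose the sizes to the enrolling investigator; in practice they should stay unpublished until enrolment closes.
3. Keep the existing order, with each assignment released only after consent and baseline.

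**Cost.** A new set of lists from a person already in the role, and a short protocol note. Under the new lists the maximum imbalance within a site is 4 instead of 2. Sizes 4 and 6 hold it to 3, with about 6% of assignments certain and 68% guessed, against about 2% and 67% for 4, 6 and 8. A block of four left open at the switch can add up to 2 at that site. The change removes nearly all certain foreknowledge but not guessing, so it should not be described as making assignments unpredictable.

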**Fig. 4 Fig4:**
[figure not shown]
Screenshot of self-monitoring calendar

A self-monitoring calendar is used as a measure to assess drug use for a period of 28-days before the baseline and for follow-up assessments like the Timeline Followback (TLFB) method [28, 29]. Web-based versions of the TLFB methods have been developed and adapted to various substances with good reliability and validity [30–32] and have been used in some intervention studies [11, 19–21].

e-SMARPP is equipped with some automated functions for participants, including progress tracking and a notification e-mail when they receive feedback. In the notification e-mails, a related webpage link is shown and users can access the webpage directly. For example, users can view the feedback comment webpage directly after they click the link in the notification e-mail. Additionally, for researchers who registered on e-SMARPP, a notification e-mail will be sent when participants submit an exercise, diary and questionnaire.

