### Data monitoring

The research members who have an e-SMARPP account (AT, YM, NK and TM) will monitor the data. The first author (AT) will manage participants’ progress and completion of the intervention and the follow-up assessments. The members will share information about recruitment progress and data collection every month.

Information of adverse events including hospitalization, arrest and death will be collected from the participants’ primary doctor during the intervention. Additionally, participants will be asked about subjective harmful effect (i.e., craving, mental distress) when they use e-SMARPP at the follow-up assessment (T2).

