### Ethics and dissemination

#### Research ethics and approval

The Ethics Committee of the Faculty of Medicine and Graduate School of Medicine of the University of Tokyo and the Ethics Committee of each recruiting hospital and clinic (National Center of Neurology and psychiatry, Saitama Psychiatric Medical Center, Kanagawa Psychiatric Center, Okayama Psychiatric Medical Center, Tokyo Metropolitan Matsuzawa Hospital and APARI clinic) approved this study. Before the baseline survey, candidates will be fully informed that their participation is totally voluntary and can withdraw the consent if they want and they can send a withdrawal e-mail to researchers and also tell their intention to withdraw to their primary doctor. Even if they withdraw the consent, they will not receive any disadvantage. In addition, they will be informed that the findings of this study will be disseminated without participants’ personal infromation via publication and website. Face-to-face informed consent will be conducted (AT) and signed consent forms will be obtained from all participants. The participants will be told that the web-based program does not provide emergency support verbally and on the website and will be encouraged to use proper medical services or talk to their primary doctor in case of an emergency. If a researcher becomes aware of an emergency condition (e.g., imminent suicide intention, violence) through e-SMARPP, the researcher will consult with the participant’s primary doctor. All data collected in this study is securely stored without the participants’ personal information (name, address, etc.). Access to the data is encrypted and limited to research staff named on the ethics protocol.

This study protocol was registered with the University Hospital Medical Information Network clinical trial registry (UMIN-CTR), number UMIN000016075. If there are important modifications of the protocol, we will obtain approval for the modifications from the Ethics Committee of the Faculty of Medicine and Graduate School of Medicine of the University of Tokyo and will revise the protocol on the UMIN-CTR website.

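### The analysis is presented as blinded to group, but one of the two analysts is the first author, who tells participants their allocation and writes most of the intervention-only feedback

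*Protocol article*

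**What the plan says.** Trial design describes the study as a "parallel-group, non-blinded and multicenter randomized controlled trial". Randomization and blinding adds two statements about masking. On the sites: "Researchers and staff who work for recruiting institutions will be blinded". On the analysis: a researcher who will not analyse downloads the data, an independent staff person masks the group variable, and the first author and a second researcher (name removed in the text available) "will analyze data that is blinded to the group variable".

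Other parts of the article assign further tasks to the first author:

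- Randomization and blinding: enrols participants and tells each one the assigned group.
- Research ethics and approval: takes consent face to face.
- Interventions: is the main writer of the tailored comments on exercises and diaries.
- Data monitoring: is one of four account holders who monitor the data, and manages participants' "progress and completion of the intervention and the follow-up assessments".

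The Interventions text on automated functions adds that, for researchers registered on the site, "a notification e-mail will be sent when participants submit an exercise, diary and questionnaire".

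**The concern.** Hiding the group label protects an analysis only if the analyst does not know the allocations by another route. Here one of the two analysts has told each participant their group and has read and answered the intervention arm's submissions. The plan's own division of roles therefore undercuts the property it claims for that analyst.

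Two things are at stake. First, a report that repeats the protocol's wording would lead readers to credit the trial with a blinded analysis when judging risk of bias. Second, some choices remain open at the analysis stage. The longest run of abstinent days is one of two primary outcomes, and Primary analysis requires both to be significant before the intervention counts as effective. A choice that moves the abstinence result can therefore decide the trial. According to Previous work, the first author also developed the program.

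**Working it through.** No figure is in dispute, so the check sets the role assignments beside the blinding claim.

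**1. Does the first author know the allocations?** Yes. Randomization and blinding says this person informs participants of their group. The knowledge comes directly from the role and does not have to be inferred from data.

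**2. Does delivery reinforce that knowledge?** Yes. Each session contains exercises and a weekly diary (Interventions, Table 1), and Control group says controls have no access to the sessions. Exercises, diaries and the comments on them therefore exist in one arm only. The first author writes most of the comments. Notifications of an exercise or diary also identify the sender's arm to any registered researcher who receives them.

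**3. Can masking the label undo this?** Not reliably. The primary analysis tests a group-by-time interaction and a between-group *t*-test, so the file must keep some group code; the label can be recoded but not removed. With two groups, linking one record to a known participant decodes the label for all records. The first author monitors the data during the trial, and the analysis needs baseline scores and daily calendar data. Recognition is therefore possible. The documents do not show that it would occur.

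**4. Where could knowledge of arm act?**

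| Element | Source | Room for analyst choice |
|---|---|---|
| SRRS score | Primary outcome: 35 items completed by the participant on the web | Little |
| SRRS model | Primary analysis: fixed and random effects listed, no imputation | Little |
| Test and decision rule | Primary analysis: *t*-test for abstinence; two-sided 5 %, both outcomes required | Little |
| Abstinent days as recorded | Interventions: participants colour their own calendar | None at entry |
| Longest abstinent run as derived | Primary outcome joins the calendar *and* the TLFB method; the Table 2 footnote says calendar *or* TLFB | Some: the two statements differ on how sources are used |
| Sensitivity analyses | Weights from pooled logistic models; two changed definitions of abstinence | Some |
| Subgroups | Subgroup analysis: five dividing factors | Some |

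The exposure lies in the last three rows. It does not reach the participants' answers.

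**The case against.** The strongest reply is that the plan takes real precautions. The person who downloads the data does not analyse, an independent person masks the group variable, there is a second analyst, and Research ethics and approval says data are stored without names or addresses. The claim can also be read literally: it is the data that are blinded, and nothing is said about what the first author already knows. The SRRS score and the primary model leave little discretion. The larger bias route, self-report by participants who know their arm, would be unchanged by a different analyst, and the Discussion acknowledges self-report as a limitation.

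Most of this stands and limits the point. It does not rescue the claim, because masking an analysis file serves to blind its analysts, and for one of them that cannot be relied on.

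A reader might infer more than the article supports:

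- *That the site-staff sentence contradicts the non-blinded label.* The qualifying clause naturally covers both researchers and staff at the recruiting sites. Blinded site personnel are compatible with a trial whose participants know their arm. The scope should be made explicit, but this is not a contradiction.
- *That the masked file reveals arm through session data.* Program completion and content usability are collected at two months, but nothing says the primary-analysis file carries them.
- *That the first author sends the reminders.* The text says only that a researcher does. The self-monitoring reminder follows the same Sunday and Monday rule in both arms.
- *That blinding fails for every account holder.* One of the four made the allocation list and is stated not to analyse, so no claim of a blinded analyst applies to that person.
- *That abstinence rules will be set with knowledge of arm.* The article does not say who sets them or when, and such rules may sit in a statistical analysis plan that is not shown.

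**Conclusion.** The point holds in a limited form. The blinded analysis that the plan claims is not secured for one of its two analysts, given the roles the plan assigns. This should be corrected, but it does not invalidate the design.

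No size of bias can be computed from the document. The reach is bounded: derivation of the longest abstinent run, the sensitivity analyses and the subgroup analyses. The SRRS result is largely protected by participant completion and a fixed model.

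The conclusion assumes that the first author carries out the roles as written and takes a working part in the analysis. It does not assume that records are in fact recognised, nor that any choice would be made in favour of the program. Whether the second analyst is independent of delivery and monitoring cannot be told. The name is removed, and setting aside the first author and the researcher who made the list leaves two of the four account holders who could be that person.

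**What to change.** In Trial design and in Randomization and blinding, state exactly who is blinded and to what: site researchers and staff are; participants, feedback providers and the first author are not. Do not describe the first author's analysis as blinded. Reconcile the *and* and *or* wording on calendar and TLFB between Primary outcome and the Table 2 footnote.

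The rest depends on the second analyst:

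- **If that person has no e-SMARPP account and no delivery role:** have them derive the abstinence outcome and run both primary analyses from code fixed before download, on a masked file without session, exercise, diary or content-usability fields. The first author sees results only after they are locked.
- **If that person holds an account or has a delivery role:** fix the derivation and analysis code before download and report the analysis as not blinded.

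The cost is some reassignment of tasks and a less favourable blinding statement. The first option needs no new staff only if the second analyst meets its condition; the second option needs none. Sample size, the choice of outcomes and participant procedures do not change.
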